**Fig. 1 Fig1:**
[figure not shown]
Team Organizational Chart and Study Sites. Steering *Committee*: Composed of the principal investigators, co-investigators, and consultants. Reviews the protocols and monitors the progress of the studies and participant safety. Ensures the research study is implemented in compliance with the protocol and that conflicts of interest and bias are minimized. Supported by sub-committees as illustrated. All protocols were approved by the Steering Committee and the Institutional Review Boards of the participating sites in Vietnam and Johns Hopkins School of Medicine, and all participants provided written informed consent. The clinical sites in Vietnam and Saudi Arabia are listed. Johns Hopkins School of Medicine serves as Data Coordinating Center. Abbreviations: DDGH-Dong Da General Hospital, IGH-Institute of Gastroenterology and Hepatology, KFSHRC-King Faisal Specialist Hospital and Research Center, KSUMC-King Saud University Medical City, MMC-Medic Medical Center, NGH-National Guard Hospital. Map Source: World map was taken from https://www.freepik.com/free-vector/illustration-of-global-icon_2687446.htm using a premium license (subscription ID: 9765e7de-0ed0-4358-b277-90cfe44e72a9) for unlimited use without attribution

### Study schedule and assessments

Figure 2 depicts the study schema. The study is planned for five years. Individuals with a liver mass ≥ 1 cm in diameter, elevated AFP (≥ 9 ng/mL), and/or elevated GALAD score (≥ -0.63) will be scanned with dynamic contrast-enhanced MRI, and a diagnosis of HCC will be made by LiRADS-5. Additionally, those who do not exhibit abnormal imaging findings, elevated AFP titer, and/or elevated GALAD score will obtain a dynamic contrast-enhanced MRI annually for five years to assess for HCC. In Vietnam, the study sites and the funds to be received for the study will be used for conducting all the tests and MRIs. National health insurance will not be used. In Saudi Arabia, national health insurance will cover the participants’ tests and MRIs.

**Fig. 2 Fig2:**
[figure not shown]
Study Schema. Patients with chronic liver diseases from hospital database of the participating sites will be screened and invited for enrollment if eligible. Next, we prospectively survey the eligible cohort of patients at risk for HCC (i.e. patients with advanced fibrosis or compensated cirrhosis and irrespective of cirrhosis etiologies), using semi-annual abdominal ultrasound and GALAD Score for five years. During the 5-year follow-up, individuals with a liver mass ≥ 1 cm in diameter and/or elevated GALAD score (≥ -0.63) will be scanned with dynamic contrast-enhanced MR,I and a diagnosis of HCC will be made by LiRADS assessment (LiRADS-5). Additionally, those who do not exhibit abnormal imaging findings and/or elevated GALAD score will obtain a dynamic contrast-enhanced MRI annually for five years to assess for HCC

During the 5-year time frame, we anticipate at least 80 (approximately 16 each year if 1% incidence x five years for both cohorts in Vietnam and Saudi Arabia) or as many as 320 (64 per year if 4% incidence x five years for both cohorts in Vietnam and Saudi Arabia) incident HCC cases given the high HCC incidence rate in Vietnam and Saudi Arabia. With the range of 80 to 320 anticipated HCC cases, we will have 90% to 99% power, respectively, to detect a meaningful difference in the cases vs. control (more on sample size calculation below). We will compare sensitivity for early HCC detection (primary outcome measures), false-positive results, and resultant diagnostic evaluation.

By leveraging the prospective cohort, we will establish a biorepository of longitudinally collected biospecimens from patients with fibrosis/cirrhosis to be used as a reference set for future research. Clinical, laboratory, and imaging data, urine, and plasma biospecimens are from participants for up to five years; data are collected only from participants who maintain the absence of evidence of HCC on imaging and/or biopsy. Biospecimens and associated de-identified clinical data from participants enrolled in this study will be stored in Vietnam for participants from Vietnam and in Saudi Arabia for participants enrolled from Saudi Arabia.

### Screening

Before or during the first visit, patients with chronic liver diseases, including advanced fibrosis/cirrhosis identified by ICD-10 from participating clinical sites, will be screened.

The screening criteria are MELD ≤ 15, non-invasive indices, and finally confirmed by Fibroscan or ARFI elastography results to further select those with fibrosis score F3 or higher from the 10 clinical centers’ databases in this Study Cohort Database (Fig. 1 & 3). All patients will be required to have a negative dynamic contrast-enhanced MRI upon study enrollment to rule out HCC before the study enrollment. Only MRI nearest to the time of GALAD score or abdominal ultrasound (US) and or AFP evaluation will be included in the analysis. If patients have a history of metal in their heads or eyes, they will need an x-ray of their skull to find out if the MRI is safe for them.

**Fig. 3 Fig3:**
[figure not shown]
Overall Patient Screening and Enrollment Flow. The study will be introduced at the 10 sites for the outpatient internal, hepatology, gastrointestinal, infectious diseases doctors, and viral hepatitis management team to ensure all the doctors approaching the target population know about the study. Prospective patients were screened for eligibility for the inclusion criteria and exclusion criteria by the study coordinators. Patients who fulfilled inclusion criteria will be introduced and explained about the study by the study coordinators and or site principal investigators. At the initial screening visit, the details of the study will be introduced. If the participant is agreeable and thought to have met the inclusion and exclusion criteria, then he/she may enter the formal study enrollment phase. The signing of the consent statement and the procedures during screening and enrollment can occur on one day or separate calendar days and may occur over a period of up to 30 days. Subsequent study follow-ups and procedures are shown

### Enrollment

The participant is considered enrolled in the study once the consent is signed and the Registration Form has been completed. Activities at the initial screening and or study registration visit include:Sign the formsSignature on the study consent and biorepository consent formSignature on the Health Insurance Portability and Accountability Act (HIPAA) authorization form for the studyAssignment of the study participant identification numberMedical and medication historyPhysical examination including vital signs, height, weight, anthropometric measurements, handgrip strength measurementScreening electrocardiogram (ECG)Acanthosis nigricans and liver signsObtaining laboratory and other information (on the co-variates list)Instructing participant to bring to initial screening visit his/her health history information or related materialsParticipant to sign medical records release to obtain study labs and imagingParticipant to provide location and contact informationCoordinator to register participants on clinic data systemCoordinator to request prior reports and study imaging/procedures from healthcare providerLaboratory testHematology (complete blood count)Chemistry (hepatic panel, hemoglobin A1c (HbA1c), fasting lipid profile and fasting glucose and insulin levels, fasting blood (plasma) for specimen bankingImaging diagnostic: abdominal ultrasound, Fibroscan, or ARFILiver biopsy (if needed)Provision of the standard of care educational materials (delay providing these to the participant until confirmed eligible for the study)Schedule for the second visit

### Participant retention & compensation

We will disseminate flyers comprising vital study information in hepatology clinics of the study sites. We also have databases of prospective study candidates at the study sites. Our strategy to recruit and follow-up the study patients to minimize the drop-out is by emphasizing the following:selecting the committed candidates by checking on their response time following the invitation and implementing an ask-back method to check for their understanding of the study,setting up patient expectations and roadmap when they join the study,individually reminding and scheduling patient follow-up appointments using automation systems,incentivizing study patients with parking lot costs (or transportation vouchers) and study tests/MRIs during the studies (all these incentives have been budgeted),sending ‘thank you’ notes to study patients after each visit to enhance the trusting relationship between the study staff and study patients.

The participants will have free laboratory tests and MRI annually. They will also be compensated for the transportation costs for 10 visits.

### Schedule of activities

Data will be collected during screening (initial visit) and at semi-annual intervals thereafter (a maximum of ten visits). Schedule of activities (Table 1) displays the data collection schedule for screening and follow-up.

**Table 1 Tab1:** Schedule of activities

Procedures	Screening/baseline (Visit 1)	Study Visit 2	Study Visit 3	Study Visit 4	Study Visit 5	Study Visit 6	Study Visit 7	Study Visit 8	Study Visit 9	Final Study Visit 10
Informed consent	X									
Demographics	X									
Home address/Phone number	X	X	X	X	X	X	X	X	X	X
Medical history	X	X	X	X	X	X	X	X	X	X
Collect and archive serum (15 mL blood, 50 mL urine)	X	X	X	X	X	X	X	X	X	X
Concomitant medication review	X	X	X	X	X	X	X	X	X	X
Physical exam (including height and weight)	X	X	X	X	X	X	X	X	X	X
Vital signs	X	X	X	X	X	X	X	X	X	X
Height	X									
Weight	X	X	X	X	X	X	X	X	X	X
Waist circumference	X	X	X	X	X	X	X	X	X	X
Performance status	X	X	X	X	X	X	X	X	X	X
Handgrip strength measurements	X	X	X	X	X	X	X	X	X	X
Hematology	X	X	X	X	X	X	X	X	X	X
Serum chemistry	X	X	X	X	X	X	X	X	X	X
Adverse event review and evaluation		X	X	X	X	X	X	X	X	X
Radiologic/Imaging assessment (Abdominal Ultrasound and/or cross section imaging if triggered)	X	X	X	X	X	X	X	X	X	X
Dynamic contrast-enhanced CT or MRI	X		X		X		X			X
Fibroscan	X									X
Complete Case Report Forms (CRFs) that have clinical data and events	X	X	X	X	X	X	X	X	X	X

### Follow-up visits

Semi-annual follow-up visits will be scheduled at 22 to 26-week intervals after enrollment. Each visit has an ideal date for a visit, a lower window date (opening date for the window), and an upper window date (closing date for the window). The dates for a specific participant are specified on their visit time windows sheet. In addition to the activities in Table 1, new procedures and forms are to be completed at each of the follow-up visits (at 6, 12, 18, 24, 30, 36, 42, 48, and 54 months) are:Follow-up medical history (medication changes, key events or interventions, surgeries)Hospital admissions, new diagnoses of co-morbidities, complications of liver disease (variceal bleeding, ascites, edema, hepatic encephalopathy), liver cancer, other cancer, diabetesPhysical examinationAbdominal US and AFPLaboratory data (hematology, glucose, insulin, clinical chemistry, hepatic panel, HbA1c, lipid profile)Blood collection for plasma bankingDocumentation of any additional liver biopsies performed

Additionally, annually, each study participant will obtain a dynamic MRI with contrast to evaluate for liver cancer.

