### Outcome measures

The primary endpoint is the performance of GALAD score determined in association with HCC detection by LiRADS criteria in a cohort with advanced fibrosis or cirrhosis (e.g., Metavir F3 or higher, with MELD 15 or lower) undergoing prospective surveillance every six months for five years. Performance of GALAD score will be determined by using the GALAD score cut-off value of -0.63 to prospectively survey a cohort of 1,600 patients with advanced fibrosis and early cirrhosis (e.g., Metavir F3 or higher, with MELD 15 or lower) for early detection of HCC by Liver Imaging Reporting and Data System (LiRADS) assessment (LiRADS-5). The GALAD cut-off value was previously determined in case–control studies [11]. For the establishment of the biorepository, the endpoint is the proportion of study participants who agree to consent for bio-specimen when invited.

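### The visit schedule stops at month 54 and Table 1 has no month-48 MRI, so the promised five years and annual MRI are not scheduled, and 80–320 expected cases become 72–288

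*Protocol article*

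**What the plan says.** **Promised duration.** The primary endpoint (Outcome measures) is set in a cohort "undergoing prospective surveillance every six months for five years". Study schedule and assessments says that participants without a trigger "will obtain a dynamic contrast-enhanced MRI annually for five years to assess for HCC", and Follow-up visits repeats that every participant has a yearly contrast MRI.

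**Scheduled duration.** Schedule of activities caps the data collection at ten visits, and screening is one of them: "Data will be collected during screening (initial visit) and at semi-annual intervals thereafter (a maximum of ten visits". Table 1 labels screening/baseline as Visit 1 and Visit 10 as final. Follow-up visits gives the nine later visits by month: "at 6, 12, 18, 24, 30, 36, 42, 48, and 54 months". Outcome ascertainment and study exit definitions ends a participant's study at the last Table 1 visit or procedure, or at HCC. Participant retention & compensation agrees with ten: "They will also be compensated for the transportation costs for 10 visits".

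**Scheduled MRI.** The Table 1 row "Dynamic contrast-enhanced CT or MRI" is marked at Visits 1, 3, 5, 7 and 10. Visits 8 and 9 are blank.

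**Planning figures.** The text below Fig. 2 expects at least 80 cases ("approximately 16 each year if 1% incidence x five years for both cohorts in Vietnam and Saudi Arabia") and up to 320 at 4% incidence, and continues: "With the range of 80 to 320 anticipated HCC cases, we will have 90% to 99% power, respectively". Sample size likewise multiplies the annual incidence by five, to 0.05 in the low case, and reports 621 and 119.

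**The concern.** The text and the schedule describe two different studies, one of 60 months with annual MRI and one of 54 months with an 18-month final MRI interval. Two things depend on which is carried out.

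The first is the case count. The power statement is tied to 80–320 cases, and those counts use six months of follow-up that no visit covers.

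The second is the reference standard. For participants with normal ultrasound, AFP and GALAD, the scheduled MRI is how a missed cancer is found, so its timing bears directly on sensitivity, the primary measure. Statistical methods keeps only the MRI nearest to each test. A site that follows Table 1 will skip the month-48 scan, and a site that follows the text will do it, so ascertainment could differ between sites.

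**Working it through.** **1. Length of follow-up.** Ten visits including baseline make nine six-month steps: 9 × 6 = 54 months = 4.5 years.

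**2. MRI schedule.**

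| Visit | 1 | 3 | 5 | 7 | 9 | 10 |
|---|---|---|---|---|---|---|
| Month | 0 | 12 | 24 | 36 | 48 | 54 |
| CT/MRI in Table 1 | yes | yes | yes | yes | no | yes |

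This gives four post-baseline scans with a last interval of 54 − 36 = 18 months. If Visit 10 were taken as month 60, against the month list, the gap would be 24 months. No reading of Table 1 gives annual MRI.

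**3. Expected cases.** Rule used in the protocol: N × annual incidence × years, with N = 1,600.

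| Annual incidence | 5 years (as stated) | 4.5 years (as scheduled) |
|---|---|---|
| 1% | 1,600 × 0.01 × 5 = 80 | 1,600 × 0.01 × 4.5 = 72 |
| 4% | 1,600 × 0.04 × 5 = 320 | 1,600 × 0.04 × 4.5 = 288 |

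The stated figures are reproduced at five years. At 4.5 years both fall by 10%.

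**4. Sample size.** The incidence proportions become 4.5 × 0.01 = 0.045 and 4.5 × 0.04 = 0.18 instead of 0.05 and 0.20. The protocol does not state the proportion compared with these. I used the two-proportion formula with continuity correction, two-sided alpha 0.05 and 90% power:

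n₀ = [1.96·√(2p̄(1−p̄)) + 1.2816·√(p₁(1−p₁) + p₂(1−p₂))]² / (p₁−p₂)²

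n = (n₀/4)·[1 + √(1 + 4/(n₀·|p₁−p₂|))]²

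| Assumption | Low incidence | High incidence |
|---|---|---|
| 5 years, doubling | 0.05 vs 0.10: 621 | 0.20 vs 0.40: 119 |
| 4.5 years, doubling kept | 0.045 vs 0.09: 695 | 0.18 vs 0.36: 137 |
| 4.5 years, absolute difference kept | 0.045 vs 0.095: 585 | 0.18 vs 0.38: 114 |

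The first row matches both stated figures exactly, so a doubling is the likely comparator, but that is an inference. Under doubling, the margin of 800 over the low-incidence requirement falls from 800 − 621 = 179 to 800 − 695 = 105 per country. Power at 800 per group, without continuity correction, goes from 96.7% to 94.9%.

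**5. Distance from test to nearest MRI.** The month-42 test is 6 months after the month-36 scan and 12 months before the month-54 scan, so it pairs with the earlier one. The month-48 test has no same-visit scan and is 6 months before month 54. The largest distance is 6 months.

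**The case against.** The strongest reply is that this is a small inconsistency with little consequence.

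- *The text already requires the month-48 scan.* Follow-up visits adds the annual MRI on top of Table 1, so the table may simply lack one mark. That is fair, but it confirms the contradiction, and the table is what sites schedule from.
- *The pairing harm is weak.* With scans at months 36 and 48, the month-42 test would be 6 months from each, so it might pair with month 36 anyway. The month-54 scan also serves as an exit scan. Both points stand. The clear loss is the same-visit scan at month 48, and triggered imaging remains available at every visit.
- *The case range is a wide bracket.* Ten per cent is small inside a fourfold range, and 80 cases in 4.5 years need only 80/(1,600 × 4.5) = 1.11% a year. The Background cites rates of up to 4% and 8%. This stands as a limit on size. Still, the protocol chose 1% as its floor and claims at least 80 there.
- *No power failure is shown.* Correct before loss: 800 exceeds every recomputed requirement. The direction of change in n also depends on the unstated comparator, rising to 695 or falling to 585.
- *72–288 is not the only possible replacement.* Also correct. Intervals of 22 to 26 weeks make nine steps 198 to 234 weeks, or about 61–72 and 243–287 cases. Counting person-years from one year after enrolment, as the exit definitions do, leaves 3.5 years, or 56 and 224. These push the count further down, so 72–288 is not a pessimistic choice.

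The protocol's multiplication is right. What is wrong is the number of years put into it.

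**Conclusion.** The point holds. The schedule delivers 54 months, not five years, and Table 1 does not deliver annual MRI. This does not come from condensing a protocol into an article, because the month list, the visit table and the arithmetic are all printed and disagree.

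On the protocol's linear rule and before loss, expected cases are 72–288 instead of 80–320, and the last MRI interval is 18 months instead of 12. The sample-size effect rests on an inferred comparator and, before loss, does not overturn 800 per country. With doubling, however, the loss that 800 can absorb at low incidence drops from 179/800 = 22% to 105/800 = 13%, whereas the Missing data section says up to 30% was allowed for. That 30% would leave 560, already below 621.

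This should be corrected, but it does not threaten the design.

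**What to change.** Choose one duration and make Table 1, Schedule of activities, Follow-up visits, Outcome measures, Study schedule and assessments (with the text below Fig. 2) and Sample size agree with it.

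**Option A, 54 months stands.** State 54 months of follow-up. Mark the month-48 MRI in Table 1, or state the 18-month final interval openly. Restate the expected cases as 72–288 before loss, use 0.045 and 0.18 in Sample size, state the compared proportion, and recompute the sample sizes and the linked power. Cost: corrections to text and table. Marking the month-48 MRI adds one scan per participant still under surveillance, at most 1,600.

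**Option B, five years is intended.** Add a month-60 visit, place MRIs at months 48 and 60 in place of month 54, and keep 80–320. Cost: one extra visit and one net extra MRI per participant (six scans including baseline instead of five). Transport compensation must then cover 11 visits instead of 10.

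Under either option, any after-loss case count should use one method with its attrition assumption stated. Neither option needs additional patients.

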### GALAD score

This study is considered a prospective observational cohort study. GALAD score, comprising Gender, Age, AFP-L3, AFP, and DCP, is an add-on test to the routine HCC surveillance care with the provisions of abdominal US and AFP every six months.

Japanese investigators have, for several decades, combined AFP with two additional markers, DCP and AFP-L3, for diagnosis and surveillance. DCP, also known as Protein Induced by Vitamin K Absence or Antagonist-II (PIVKA-II) is an immature form of prothrombin [12, 13]. Elevated DCP values (≥ 7.5 ng/ml) are associated with a fivefold increased risk of developing HCC, and on this basis, DCP has received USFDA approval for risk assessment. AFP-L3, a glycoprotein normally produced by the fetal liver, is one of three AFP glycoforms that can be separated based on their lectin binding characteristics, most readily with LCA. An increase in AFP-L3 appears more specific for HCC than total AFP in adults. It is usually presented as a percentage of the total AFP with a reference range of < 10%.

GALAD formally combines these three serum biomarkers together with age and gender to produce an algorithm with better performance than its individual constituents. The GALAD model is of the form: Z = -10.08 + 0.09 × age + 1.67 × sex + 2.34 log (AFP) + 0.04 × AFP-l3 + 1.33 × log (DCP). Where sex = 1 for males, 0 for females.

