A patient who meets any of the following criteria will be excluded from participation in this study:Decompensated cirrhosis (variceal bleeding, hepatic encephalopathy, ascites, spontaneous bacterial peritonitis, and/or hepatorenal syndrome) or MELD > 15Individuals who already have HCC, with or without HCC treatmentOn liver transplantation list or anticipated to be on the liver transplantation list during the study durationAny serious or active medical or psychiatric illness that, in the opinion of the investigator, would interfere with patient treatment, assessment, or compliance with the protocolKnown HIV positive statusTaking Vitamin K within seven days prior to clinic follow or having disease affecting Vitamin K levels.Active drug use or dependence that, in the opinion of the study investigator, would interfere with adherence to study requirementsInadequate documentationIndividuals who cannot, do not want to, or refuse to sign the informed consent form

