### Statistical methods

Bootstrap resampling technique will be used to account for repeated measures to estimate standard errors and confidence intervals. Only MRI nearest to the time of GALAD, US and/or AFP evaluation will be included in the analysis. For time-to-event data, we will use the Cox proportional hazards regression model with covariates tailored to the hypothesis under investigation. For hypotheses involving repeated measurements, events, counts, or other discrete responses, we will use either of two approaches: (1) generalized linear models with generalized estimating equations with robust variance estimation to account for the clustering, or (2) multilevel generalized linear mixed models with random coefficients to account for within-patient clustering as well as other sources of variations like clinic effects.

We will include a random intercept for each hospital site to account for variability by facility. Stratified analyses will be presented for p for interaction < 0.2. Demographic and clinical characteristics will be summarized with proportions and median (minimum–maximum) with no calculation of p-values as this is a non-randomized study. Age at liver disease diagnosis and sex will be accounted for in all analyses. Other confounders of interest include interval follow-up and insurance coverage, whereas age and gender are already controlled in the GALAD (gender, age, etc.) score calculations. All statistical analyses will be performed in SAS 9.4 (or R or another statistical software package with equivalent capabilities).

Baseline descriptions of patients with the standard of care (US and AFP) vs. GALAD score will be compared to each other. Other baseline demographics, biochemical lab results, MRI results, Fibroscan, and abdominal US in the cohort will also be described.

The interim analyses will re-evaluate the performance of the GALAD cut-off score of -0.63 after year 2 of the study. The interim analyses will not be used to assess for study events (i.e., HCC cases), and thus there will be no plan to stop the study if there were no number of events (i.e. HCC cases).

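### The vitamin K exclusion leaves out vitamin K antagonists, its timing during follow-up is unclear, and no stated rule handles a GALAD result taken under such exposure

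*Protocol article*

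**What the plan says.** - **Eligibility criteria, exclusion list.** The list opens with "A patient who meets any of the following criteria will be excluded from participation in this study". One entry covers vitamin K intake in the seven days before a clinic follow, a term the article does not define, or a disease affecting vitamin K levels. Neither this entry nor any other names an antagonist or anticoagulant.
- **GALAD score.** The marker's name is spelled out: "DCP, also known as Protein Induced by Vitamin K Absence or Antagonist-II (PIVKA-II) is an immature form of prothrombin". DCP enters the equation with coefficient 1.33 on the log scale. The base of the logarithm is not stated.
- **Outcome measures.** Performance is judged by "using the GALAD score cut-off value of -0.63 to prospectively survey a cohort of 1,600 patients". An elevated score also triggers MRI (Study schedule and assessments).
- **Schedule of activities, Table 1.** "Concomitant medication review" is marked at all ten visits. Follow-up visits also asks about medication changes.
- **Statistical methods.** The stated limit on the data concerns imaging: "Only MRI nearest to the time of GALAD, US and/or AFP evaluation will be included in the analysis". On adjustment: "Other confounders of interest include interval follow-up and insurance coverage". Drug exposure is not listed.

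**The concern.** The exclusion shows that the sponsor regards vitamin K status as able to distort DCP, and therefore GALAD. An antagonist drug is neither vitamin K intake nor a disease. The rule thus omits the one drug exposure that the marker's own name gives as a cause.

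The rule is also worded as exclusion of a patient, while GALAD is measured semi-annually for five years. If someone starts an antagonist or receives vitamin K in year 3, the article does not say what happens to that GALAD result.

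The accuracy of GALAD at -0.63 is at stake. A positive caused by an antagonist in a patient without a tumour counts as a false positive, can recur while the drug continues, and leads to MRI each time. In a patient with HCC, the same effect would flatter sensitivity. Recent vitamin K intake could act in the opposite direction. The article intends to compare sensitivity, false-positive results and the resulting diagnostic work-up, so all of these matter to it.

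**Working it through.** The article gives no figure on this point, and its sample sizes (621 and 119) are unaffected. Three checks follow.

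**1. Scope and timing of the rule**

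| Exposure | Exclusion list | Stated handling of the GALAD result |
|---|---|---|
| Vitamin K intake | Covered, seven days before a clinic follow | None |
| Disease affecting vitamin K levels | Covered, no time limit | None |
| Vitamin K antagonist | Not mentioned | None |

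The first row can be read in two ways. Its place in the exclusion list suggests entry, while its time anchor suggests each follow-up visit. On the second reading, the consequence given is exclusion of the patient, and nothing is said about the result. Variables assessments and definition also allows the entry GALAD to use results up to six months old, so a seven-day window before a visit need not cover that blood draw. Antagonists are uncovered on either reading.

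**2. Can DCP alone change a result?**

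Equation (GALAD score section): Z = -10.08 + 0.09 × age + 1.67 × sex + 2.34 log(AFP) + 0.04 × AFP-L3 + 1.33 log(DCP).

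A k-fold rise in DCP shifts Z by 1.33 × log(k). For k = 10:
- base 10: 1.33 × 1 = 1.33
- natural log: 1.33 × 2.303 = 3.06

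Illustration, assuming base 10, AFP 4 ng/mL, AFP-L3 1% and DCP in ng/mL. For a man of 60 at DCP 1:

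Z = -10.08 + 5.40 + 1.67 + 2.34 × 0.602 + 0.04 + 0 = -1.56

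At DCP 7.5, the level the article calls elevated, add 1.33 × 0.875 = 1.16, giving -0.40. The DCP at which a patient crosses is 10^((-0.63 - Z at DCP 1)/1.33).

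| Patient | Z at DCP 1 | Z at DCP 7.5 | DCP needed to reach -0.63 |
|---|---|---|---|
| Man, 50 | -2.46 | -1.30 | 23.8 |
| Man, 60 | -1.56 | -0.40 | 5.0 |
| Man, 70 | -0.66 | 0.50 | 1.1 |
| Woman, 50 | -4.13 | -2.97 | 429 |
| Woman, 60 | -3.23 | -2.07 | 90 |
| Woman, 70 | -2.33 | -1.17 | 19 |

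The men of 60 and 70 cross and the others do not. With natural logs the AFP term changes too (2.34 × 1.386 = 3.24). The man of 60 is then already above the cut-off at DCP 1 (0.27), and the woman of 60 moves from -1.40 to 1.28. Which patients cross therefore depends on the base, but on either base a DCP rise alone changes some results and not others.

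**3. Possible size for specificity**

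Loss = u × (F1 - F0), where u is the share of HCC-free GALAD results taken on an antagonist, and F1 and F0 are the false-positive rates with and without it. The article gives none of these. Assumed: u from 0.5% to 5%, F1 from 50% to 100%, F0 = 10%.

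| u | F1 = 50% | F1 = 100% |
|---|---|---|
| 0.5% | 0.005 × 0.40 = 0.2 points | 0.005 × 0.90 = 0.45 points |
| 1% | 0.4 | 0.9 |
| 2% | 0.8 | 1.8 |
| 5% | 2.0 | 0.05 × 0.90 = 4.5 points |

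The effect on sensitivity is not quantified. The article gives nothing on exposure among HCC cases.

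**The case against.** **The rule may already act at every visit.** A reader might infer that the vitamin K rule works at entry only. The text does not support that: the window is tied to a clinic follow, which may mean each visit. This objection stands, and only the ambiguity can be claimed. It does not help with antagonists.

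**Silence is not an analysis rule.** A reader might also infer that drug-driven results are bound to enter the accuracy estimates. This is a condensed article, the full protocol and SAP are not shown, and medication is recorded at every visit, so handling may be set elsewhere. That stands as far as it goes. The point here concerns an eligibility rule that is printed, and whose scope does not match the article's own description of the marker.

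**The size is assumed.** This stands in full. The article gives neither the frequency of antagonist use nor its effect on DCP. The MELD limit includes INR and may keep out some users at entry, although as an entry criterion it does not address exposure that begins later. In the base-10 illustration the women do not cross at DCP 7.5.

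**Leaving out exposed results may itself mislead.** The Background describes GALAD applied in real time, with positives worked up. A primary analysis that drops positives which did lead to MRI could overstate specificity in use. This is a fair objection, and it is why both sets of estimates should be reported.

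**Conclusion.** The point holds in a limited form. The exclusion covers vitamin K intake and vitamin K disease but not antagonists, although the same article names an antagonist as an inducer of DCP. Its timing is unclear, and no stated rule deals with an exposed GALAD result. Followed as printed, the text would count such a result at face value.

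The firm number is the weight of DCP in the score: 1.33 per tenfold rise (base 10) or 3.06 (natural log), enough to move some patients across -0.63. The loss of 0.2 to 4.5 points of specificity rests wholly on assumed exposure and false-positive rates. The low end is more likely, because the top requires both 5% exposure and a positive result in every exposed patient. The documents do not show that the estimates will be materially biased, and that should not be inferred.

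**What to change.** 1. Reconcile the vitamin K entry in Eligibility criteria with the description of DCP in GALAD score. State whether antagonists fall within its scope, and whether it applies at entry, at each visit, or both. Which clinical rule is right is for the sponsor to decide.
2. Use the concomitant medication review in Table 1 to flag each GALAD result taken on a vitamin K antagonist or within seven days of vitamin K intake.
3. Pre-specify that sensitivity and specificity at -0.63 are reported both with all results and without the flagged ones, together with the number flagged.

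The cost is a clarified criterion and one extra analysis on slightly fewer results. Medication is already reviewed at every visit; the form needs to capture these drugs and the date of last vitamin K intake. MRI triggers and patient care do not change, so MRIs prompted by exposed results will still take place. The two sets of estimates will show whether exposure matters.
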